### Criteria for withdrawal

Participants will be excluded from the study if they fail to attend either their baseline assessment or withdraw prior to the commencement of the immediate *Sports Stars* group. Primary analysis will use the intention to treat principle, using the last observation carried forward for participants who withdraw after commencement of intervention in the immediate *Sports Stars* group.

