### Recruitment

#### Sample size

According to CONSORT guidelines, sample size calculations are based on adequate power for comparison between the effects of the *Sports Stars* program compared to standard care using the COPM immediately post intervention (T2). Data from a previous study investigating the effects of an exercise group aiming to improve physical activity, balance and strength in ambulant children with CP (6–14 years) showed a standard deviation of 1.87/2.88 (intervention/control) [32]. This standard deviation and a mean change of 2 points for performance on the COPM (clinically meaningful difference) were used to calculate sample size. Based on significance (alpha) of 0.05 and 80% power, a minimum sample of 25 participants in each group (50 participants total) will be required. Therefore, 60 participants (30 in each group) will be recruited to allow for 20% attrition.

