## Analyses

Statistical analysis will be performed using SPSS statistical software. Primary analysis will use the intention to treat principle, using the last observation recorded for participants who withdraw from the program.

Baseline data will be reported using descriptive statistics for each variable (individual sports related activity and participation goals, GM capacity, aerobic fitness, anaerobic fitness and agility, functional strength, participation and quality of life) to establish any difference between randomised groups. The method of aggregation will depend on the normality of the data and will include the mean and standard deviation (normally distributed data) or the median and interquartile range (non-normally distributed data). If characteristics are not comparable at baseline, they will be modelled as covariates in subsequent analyses in order to adjust their possible confounding effects. Linear mixed models will be used to evaluate the effectiveness of the *Sports Stars* intervention compared to the waitlist control on the primary outcome (COPM). Linear mixed models take into account variation in individuals over time, are able to manage missing data without excluding participants for further analysis and examine changes in the outcomes over time as well as across the two groups. Significance will be set at *p* < 0.05. Residuals of the fitted models will be examined to ensure that all required assumptions are met.

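### The primary COPM analysis carries the last observation forward for withdrawals, which overrides the mixed model's own handling of their missing data and can bias the T2 effect in either direction

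*Protocol article*

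**What the plan says.** Three statements in the protocol article bear on missing COPM scores.

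- Criteria for withdrawal: "Primary analysis will use the intention to treat principle, using the last observation carried forward for participants who withdraw after commencement of intervention". The sentence goes on to specify the immediate *Sports Stars* group. Children who withdraw before that group starts are excluded, not imputed.
- Analyses: "Primary analysis will use the intention to treat principle, using the last observation recorded for participants who withdraw from the program". The same rule appears a second time, with withdrawal now tied to the program.
- Analyses, a few sentences later: "Linear mixed models will be used to evaluate the effectiveness of the" intervention against the waitlist control on the COPM. One reason given for the model is that such models "are able to manage missing data without excluding participants for further analysis".

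The Sample size section sizes the trial on the comparison "compared to standard care using the COPM immediately post intervention (T2"). It allows for 20% attrition overall and does not split this by arm or by time point. Outcomes are scheduled for all participants at T1 (baseline), T2 (2 months) and T3 (5 months). The article gives no reason for LOCF and names no sensitivity analysis for missing data.

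**The concern.** A likelihood-based mixed model uses whatever scores each child has and needs no filled-in values. Once LOCF has supplied a withdrawn child's T2 and T3 scores, the model has nothing left to manage for that child. The property cited in its favour is unused exactly where most of the missing data would be expected.

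The consequence is sharpest at T2. The only earlier assessment is T1, so a child lost between the start of the group and T2 gets the baseline score again. That is a COPM change of exactly zero, analysed as if measured. The estimated effect then mixes the true effect with the dropout rate in each arm. One arm attends weekly sessions while the other waits, so equal dropout cannot be taken for granted. Intention to treat requires analysis by randomised arm; it does not require LOCF.

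**Working it through.** **Inputs from the article (Sample size).** Difference 2 points; SDs 1.87 (intervention) and 2.88 (control); alpha 0.05; 80% power; 25 per group needed; 30 per group recruited; 20% attrition.

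**Assumptions, not in the article.** Two-sided test; the SDs apply to change from baseline; all loss occurs between the start of the group and T2; dropout is unrelated to outcome; clustering within groups is ignored; dropout by arm and control gain g are as stated in each case.

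**The plan's own figure.** Pooled SD = √((1.87² + 2.88²)/2) = 2.428. The t test gives 79.8% power at 24 per group and 81.4% at 25, so the stated 25 reproduces.

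**Expected LOCF estimate.** Let d₁ and d₂ be the loss in the immediate and waitlist arms. Mean changes are 2 + g and g, and each lost child contributes zero:

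LOCF estimate = (1 − d₁)(2 + g) − (1 − d₂)g

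**Variance under LOCF.** For an arm with mean m, SD s and loss d: (1 − d)s² + d(1 − d)m², divided by the full 30. On observed data it is s² divided by 30(1 − d). Power uses the noncentral t with unequal variances.

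**Worked case, 20% loss in both arms, g = 1.**
- Estimate: 0.8 × 3 − 0.8 × 1 = 1.6.
- LOCF variances: 0.8 × 3.497 + 0.16 × 9 = 4.24 and 0.8 × 8.294 + 0.16 × 1 = 6.80. SE = √((4.24 + 6.80)/30) = 0.61.
- Observed data: SE = √((3.497 + 8.294)/24) = 0.70.

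**Range (true difference 2.0 throughout).**

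| Loss immediate / waitlist | g | LOCF estimate | SE, LOCF vs observed | Power, LOCF vs observed |
|---|---|---|---|---|
| 20% / 20% | 1 | 1.6 | 0.61 vs 0.70 | 74% vs 79% |
| 20% / 20% | 0 | 1.6 | 0.58 vs 0.70 | 77% vs 79% |
| 10% / 10% | 1 | 1.8 | 0.62 vs 0.66 | 81% vs 84% |
| 20% / 10% | 1 | 1.5 | 0.63 vs 0.67 | 65% vs 83% |
| 20% / 0% | 1 | 1.4 | 0.65 vs 0.65 | 57% vs 86% |
| 0% / 20% | 1 | 2.2 | 0.59 vs 0.68 | 96% vs 82% |
| 0% / 20% | 0 | 2.0 | 0.58 vs 0.68 | 92% vs 82% |

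Simulation (40,000 trials, 30 per arm) agrees. At 20% loss in both arms with g = 1, the mean estimate is 1.60 and the 95% interval covers the true 2.0 in about 90% of trials. Observed data give 2.00 and 95%.

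**No true effect.** With equal 20% loss and both arms gaining 1 point, the estimate is unbiased and the type I error is 5.1%. With a deliberately uneven 5% and 35% loss and the same gains, the estimate is 0.95 − 0.65 = +0.30 and the type I error is 9.0%.

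**The case against.** Several points on the other side stand.

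- A reader might infer that the two rules are incompatible, or that LOCF leaves nothing missing. The text does not support that. LOCF is limited to children who withdraw. A child who stays in the trial but misses a visit or an instrument is still handled by the mixed model, so both rules can be carried out together. The fair charge is a poor and unexplained combination.
- A reader might also infer from the Analyses wording, "using the last observation recorded for participants who withdraw from the program", that a child who stops sessions is imputed instead of assessed. No section states this. Criteria for withdrawal speaks of leaving the study, and T2 and T3 are scheduled for all participants. It is an ambiguity to settle.
- The 20% attrition is not stated to fall before T2. Follow-up runs to T3, and losses after T2 leave the T2 comparison untouched by LOCF. Going from 30 to 25 per group is a 16.7% loss, which gives 1.67 instead of 1.6.
- Equal dropout pulls a real benefit toward zero, which is conservative for a superiority claim, and the power cost is then only 2 to 6 points in the cases above. The exaggeration to 2.2 needs a control gain as well as waitlist-only loss.
- Calling the precision invented overstates it. The LOCF standard error describes the spread of the LOCF estimate correctly (0.603 against 0.605 in simulation). What it leaves out is uncertainty about the unseen scores. The reduction against observed data is about 13% at 20% loss in both arms and about 7% in the 20%/10% case.

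None of this supplies a reason for LOCF in the primary analysis. The conservatism argument also fails once dropout differs between arms.

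**Conclusion.** The point holds and should be fixed. The article fixes LOCF for withdrawals in the primary analysis in two places, without a reason, beside a model chosen partly because it does not need it. For a child lost between the start of the group and T2, the rule asserts a zero COPM change and treats it as data.

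Under the stated assumptions, a true difference of 2.0 is estimated anywhere from 1.4 to 2.2 in the cases shown, with power from 57% to 96% against 79% to 86% on observed data. The article fixes neither the size nor the direction, because it gives no dropout by arm, no timing and no expected control gain. The estimate is unbiased with waitlist-only loss and no control gain, and with equal dropout and no true effect. The T2 comparison is unaffected if losses come after T2. The observed-data figures stand in for the mixed model when dropout is unrelated to outcome. The model itself is valid more widely, under missing at random, but not under every mechanism.

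**What to change.** Delete LOCF from Criteria for withdrawal and from Analyses. State that the primary analysis is the linear mixed model fitted to all observed T1, T2 and T3 COPM scores, by randomised arm, under a missing-at-random assumption. If a single imputation is wanted, keep LOCF or a delta-adjusted imputation as a labelled sensitivity analysis.

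Add one sentence saying that withdrawal from sessions is not withdrawal from assessment, so the T2 and T3 visits already scheduled for all participants are still sought and used.

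The cost is a few sentences of wording, plus the effort of bringing children who stop sessions to visits already planned. The downsides are a slightly larger standard error (for example 0.70 instead of 0.61 at 20% loss in both arms with a 1-point control gain) and reliance on missing at random, which the sensitivity analysis should probe.

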### Recruitment

#### Sample size

According to CONSORT guidelines, sample size calculations are based on adequate power for comparison between the effects of the *Sports Stars* program compared to standard care using the COPM immediately post intervention (T2). Data from a previous study investigating the effects of an exercise group aiming to improve physical activity, balance and strength in ambulant children with CP (6–14 years) showed a standard deviation of 1.87/2.88 (intervention/control) [32]. This standard deviation and a mean change of 2 points for performance on the COPM (clinically meaningful difference) were used to calculate sample size. Based on significance (alpha) of 0.05 and 80% power, a minimum sample of 25 participants in each group (50 participants total) will be required. Therefore, 60 participants (30 in each group) will be recruited to allow for 20% attrition.

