#### Recruitment process

Eligible children will be prospectively recruited through the client database of a state-wide community rehabilitation service. As geographical location and participant availability are critical to forming groups of sufficient participant numbers for this study, participants will be recruited in blocks according to their geographical location. Once at least four, and a maximum of six, children are identified that can attend an eight-week group on a specified day in a specific geographical location, these children will be assigned as group one. When a second group of four to six children are identified for a geographical location, they will be assigned as group two. When two groups of four to six participants each are identified, they will proceed to randomisation.

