#### Randomisation

A random sequence will be generated via coin flip by an independent, off-site co-investigator (MA) who will not be involved with assessment or treatment (as per process used in previous studies [17]). The outcome (heads: group 1 = immediate *Sports Stars* intervention, group 2 = waitlist *Sports Stars* intervention. Tails: group 1 = waitlist *Sports Stars* intervention, group 2 = immediate *Sports Stars* intervention) will be written on a piece of paper and concealed inside a sequentially numbered, opaque envelope and stored securely off-site.

When two groups are identified, they will be randomly assigned to either the immediate intervention group or the waitlist control group with a 1:1 block allocation via drawing of one of the opaque envelopes. Randomisation will be completed offsite by the same independent co-investigator (MA). This process will continue until 60 participants complete baseline assessments and proceed to the *Sports Stars* group.

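### The stated 80% power with 25 children per arm assumes individually randomised children, but the trial randomises intact groups of four to six.

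*Protocol article*

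**What the plan says.** The Sample size section of the protocol article bases the calculation on COPM performance at T2. A previous exercise-group study "showed a standard deviation of 1.87/2.88 (intervention/control"), and the target difference is 2 points. "Based on significance (alpha) of 0.05 and 80% power", it concludes that "a minimum sample of 25 participants in each group (50 participants total) will be required". The only inflation is for loss to follow-up: "60 participants (30 in each group) will be recruited to allow for 20% attrition".

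The Recruitment process section says that "participants will be recruited in blocks according to their geographical location". Four to six children who can attend on one day at one location form a group, and a second such group is then formed for a location. Under Randomisation, one concealed coin-flip result sends one whole group of the pair to immediate Sports Stars and the other to the waitlist. "This process will continue until 60 participants complete baseline assessments and proceed to the" Sports Stars group. Under Sports Stars intervention, each group has one lead physiotherapist.

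**The concern.** The unit of randomisation is the group, while the sample size is worked out as if each child had been randomised separately. Children in one group share a location and an attendance day and, in the immediate arm, a therapist and sessions, so their COPM changes may be correlated. Correlation inflates the variance of the difference between arms. Separately, a test that respects the allocation rests on about 10 to 14 groups and not on 50 children, which costs degrees of freedom even when the correlation is zero. The Sample size section gives no ICC, design effect, group size or number of groups.

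At stake is how the primary result is read. If the trial finds no significant difference, readers will take the chance of having missed a true 2-point benefit to be 20%. If that chance is in fact nearer 30%, a null result is weaker evidence than the protocol implies.

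**Working it through.** **Inputs from the Sample size section:** SDs 1.87 and 2.88; difference 2; alpha 0.05 (sidedness not stated; two-sided reproduces the figure, while one-sided needs only 19 per arm); 25 per arm needed, 30 per arm recruited.

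**Inputs from the Recruitment process and Randomisation sections:** groups of 4 to 6, randomised in twos, 60 children in total. That gives 60/6 = 10 to 60/4 = 15 groups, hence 10, 12 or 14 because groups come in pairs. The central case is 12 groups of 5.

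**Assumed:** ICC from 0 to 0.20. The document gives none.

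**Step 1: the plan's own figure.**
- Pooled SD = √((1.87² + 2.88²)/2) = 2.43; standardised difference 2/2.43 = 0.82.
- Normal approximation: n = 2 × (1.960 + 0.842)² × 2.43²/2² = 23.1, so 24 per arm.
- Noncentral t on 2n − 2 df: 79.8% power at 24 per arm, 81.4% at 25.

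So 25 is exactly the answer for independent children, with nothing added for group allocation.

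**Step 2: add the clustering.**
- Design effect DE = 1 + (m − 1) × ICC, with m the mean analysed group size.
- SE = √(2 × SD² × DE/n); noncentrality = 2/SE.
- Power from the noncentral t distribution, on group-level df (groups − 2 = 10) or individual-level df (children − 2).

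For 50 analysed, m = 50/12 = 4.17. Example at ICC 0.05: DE = 1 + 3.17 × 0.05 = 1.16; SE = 0.687 × √1.158 = 0.739; noncentrality = 2/0.739 = 2.71.

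| ICC | DE | Noncentrality | Power, 10 df | Power, 48 df | Difference detectable with 80% power (48 df to 10 df) |
|---|---|---|---|---|---|
| 0 | 1.00 | 2.91 | 74.7% | 81.4% | 1.96 to 2.14 |
| 0.01 | 1.03 | 2.87 | 73.4% | 80.2% | 1.99 to 2.17 |
| 0.05 | 1.16 | 2.71 | 68.5% | 75.5% | 2.11 to 2.30 |
| 0.10 | 1.32 | 2.54 | 62.9% | 70.1% | 2.25 to 2.45 |
| 0.20 | 1.63 | 2.28 | 53.9% | 60.8% | 2.51 to 2.73 |

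**Step 3: all 60 analysed** (m = 5, 10 or 58 df).

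| ICC | DE | Power, 10 df | Power, 58 df |
|---|---|---|---|
| 0.01 | 1.04 | 80.5% | 86.8% |
| 0.05 | 1.20 | 74.7% | 81.7% |
| 0.10 | 1.40 | 68.2% | 75.5% |
| 0.20 | 1.80 | 57.4% | 64.7% |

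**Step 4: other numbers of groups**, 50 analysed, ICC 0.05, same formulas.
- 10 groups: m = 5, DE = 1.20, power 64.5% (8 df) to 74.1% (48 df).
- 14 groups: m = 50/14 = 3.57, DE = 1.13, power 71.1% (12 df) to 76.6% (48 df).

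**Step 5: is the attrition margin spare?** 60 × 0.80 = 48, already below the stated minimum of 50. If 20% are lost, there is nothing left to pay for clustering.

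**The case against.** There are four serious objections.

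- **Clustering may affect mainly one arm.** Up to T2, waitlist children receive standard care from their usual therapists, typically one to one, so shared delivery exists only in the immediate arm, which also has the smaller SD. Inflating only that arm (6 groups, Satterthwaite df) gives 79.7%, 78.1%, 76.1% and 72.2% power at ICC 0.01, 0.05, 0.10 and 0.20 with 50 analysed, and 86.5%, 84.7%, 82.5% and 78.0% with 60. This stands as a milder scenario, and the two-arm figures are the heavier end. But waitlist groups still share location and day, and at 25 per arm even this model stays below 80% at every ICC shown.
- **About 60 may be analysed.** Withdrawals after the start are carried forward, so the primary analysis could retain nearly all recruits. At ICC 0.05 the two-arm range then straddles 80%. This stands, but the protocol ties its 80% to 25 per arm and sets the extra children aside for attrition. At ICC 0.10 with both arms clustered, 60 is still short on either df.
- **Pairing by location could recover variance.** It could, but it also costs degrees of freedom. With 6 pairs there are 5 df, giving 58.6% at ICC 0.05 with 50 analysed and no credit for pairing. The net effect is unknown, and the protocol claims none.
- **The ICC is unknown, and much of the loss at small ICC comes from df.** Both are true. At ICC 0.01 on 48 df, power is 80.2%. The size of the shortfall is therefore uncertain; the mismatch between calculation and design is not.

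**Conclusion.** The concern holds. The arithmetic behind 25 per arm is right for individually randomised children, but this trial does not randomise children individually, so the 80% claim is unsupported as written. With 12 groups, 50 analysed and both arms clustered, power for 2 points is about 68 to 76% at ICC 0.05 and 63 to 70% at ICC 0.10. The chance of missing a true 2-point difference is then 24 to 32% and 30 to 37%, against the 20% implied. The difference detectable with 80% power is 2.1 to 2.3 and 2.25 to 2.45 points.

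These figures rest on an assumed ICC, equal group sizes, no gain from pairing and a two-sided 5% test. About 80% is reached at 25 per arm only if the ICC is near 0.01 or less and individual-level df are used. It is exceeded with all 60 analysed if the ICC is about 0.01, or if clustering is confined to the immediate arm and the ICC does not exceed 0.10.

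**What to change.** Keep the 60 children and rewrite the Sample size paragraph as a cluster design. State the number of groups, the mean group size, the assumed ICC with its justification, the design effect 1 + (m − 1) × ICC, the degrees of freedom (matching the planned analysis, including how it treats the therapy group and the pair), and the resulting power or detectable difference for both 50 and 60 analysed children. Remove the unqualified 80%. Suggested wording:

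*Groups of four to six children are the unit of randomisation. With 12 groups and an assumed ICC of 0.05 (range 0.01 to 0.10), power to detect a 2-point difference at two-sided 5% is about 68 to 76% if 50 children are analysed and 75 to 82% if 60 are analysed (group-level to individual-level degrees of freedom).*

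If clustering is argued to arise only in the immediate arm, say so and give that calculation as well.

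The cost is one rewritten paragraph and a less favourable stated power. No extra participants are needed and no trial procedure changes. If the investigators prefer to keep 80%, the design effect alone at m = 5 takes 25 per arm to 25 × 1.20 = 30 at ICC 0.05 and 25 × 1.40 = 35 at ICC 0.10. Allowing for 20% attrition, 30/0.8 = 38 and 35/0.8 = 44 per arm would have to be recruited, before any df penalty.

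### Recruiting 60 does not cover 20% attrition from a required 50: a 20% loss leaves 48 children (24 per arm), below the stated minimum of 25 per arm

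*Protocol article*

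**What the plan says.** The Sample size section of the protocol article bases the calculation on the Canadian Occupational Performance Measure (COPM) immediately after the intervention (T2). It takes standard deviations of 1.87 (intervention) and 2.88 (control) from an earlier exercise-group study, and "a mean change of 2 points for performance on the COPM (clinically meaningful difference) were used to calculate sample size". The error rates are given as: "Based on significance (alpha) of 0.05 and 80% power". The result is that "a minimum sample of 25 participants in each group (50 participants total) will be required". The next sentence adds the allowance for loss: "Therefore, 60 participants (30 in each group) will be recruited to allow for 20% attrition".

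Two other sections bear on how the 60 are counted and what happens to children who leave. Under Randomisation, the article says: "This process will continue until 60 participants complete baseline assessments and proceed to the *Sports Stars* group". Under Criteria for withdrawal, the primary analysis is by intention to treat, "using the last observation carried forward for participants who withdraw after commencement of intervention in the immediate *Sports Stars* group".

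**The concern.** The section fixes three quantities: the number needed (50), the number recruited (60) and the share that may be lost (20%). Any two of them determine the third, and the three stated values do not fit together. Attrition is a loss from the children who enter, so the number to recruit is the number needed divided by the proportion retained. Multiplying the number needed by one plus the attrition rate gives too few.

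What is at stake is whether the sample-size statement is correct. It tells the reader that the trial keeps its minimum of 25 per arm if one child in five is lost, and that is not so.

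**Working it through.** **Inputs** (all from the Sample size section unless noted)

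- Difference to detect: 2 COPM points
- Standard deviations: 1.87 and 2.88
- Alpha 0.05 and power 80%. The article does not say whether the test is one- or two-sided. Two-sided is assumed because it reproduces the stated number; a one-sided test by the normal approximation would need only 19 per arm.
- Allocation 1:1 (Randomisation section)
- Required: 25 per arm, 50 in total
- Recruited: 30 per arm, 60 in total
- Attrition: 20%

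**Step 1: reproduce the required number.**
Pooled SD = √[(1.87² + 2.88²)/2] = √[(3.4969 + 8.2944)/2] = 2.428.
The two-sample t-test with a difference of 2 solves at 24.14 per arm, which rounds up to 25. The unequal-variance (Welch) t-test also needs 25. The stated minimum of 25 per arm is therefore right, and the problem lies only in the attrition step.

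**Step 2: reproduce the recruited number.**
- Required × (1 + attrition) = 50 × 1.20 = 60. This matches the article.
- Required ÷ (1 − attrition) = 50 ÷ 0.80 = 62.5, so 63. By arm, 25 ÷ 0.80 = 31.25, so 32 per arm and 64 in total. Neither matches the article.

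**Step 3: what 60 delivers.**
- Remaining after 20% loss: 60 × 0.80 = 48, or 24 per arm if losses are equal. This is 2 children below the stated minimum of 50.
- Largest loss that leaves 50: (60 − 50)/60 = 16.7%, or 10 children.

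**Step 4: power under the plan's own inputs.**

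| Children per arm | t-test, pooled SD | Welch t-test | Normal approximation |
|---|---|---|---|
| 24 (20% lost) | 79.8% | 79.5% | 81.4% |
| 25 (stated minimum) | 81.4% | 81.2% | 83.0% |
| 30 (no loss) | 88.0% | 87.9% | 89.1% |

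At 24 per arm the shortfall from 80% is 0.2 to 0.5 percentage points by t-test.

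**The case against.** The arithmetic is not in dispute. The case against concerns how much it matters.

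- **Power is barely touched.** At 24 per arm it rounds to 80%, and the normal approximation puts the requirement at 24 per arm. This stands as a statement of size. It does not rescue the sentence, because the article sets its own minimum at 25 per arm, which is the t-test answer, and 20% loss goes below it.
- **The analysis keeps children who withdraw.** The article carries the last observation forward, and its Analyses section uses linear mixed models that do not drop participants with missing data. So 48 is the number of children with observed T2 data, not necessarily the number analysed. That distinction is fair. But a child who leaves before T2 has only a baseline value to carry forward, which adds no observed change, and the Sample size section itself sets attrition against a minimum of 50.
- **Losses before the start are replaced.** Randomisation continues until 60 have completed baseline and proceeded, so early losses do not use up the allowance. This is correct, and it means that the allowance must cover losses from those 60 afterwards.
- **Recruitment may overshoot.** Children enter as pairs of groups of four to six, 8 to 12 at a time. With groups of four throughout, the total would reach 64. With groups of five or six it would stop at exactly 60. An overshoot is possible but not planned.
- **The 20% might be meant as a share of the 50.** Nothing in the article defines it that way, and the sentence attaches it to the children recruited.
- **The multiplication by 1.2 is inferred.** The article shows no working. It is the likely explanation because it gives 60 exactly, but the contradiction does not depend on how 60 was reached.

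**Conclusion.** The concern holds. With 50 required, recruiting 60 covers 16.7% attrition and not 20%; a 20% loss leaves 48. A true 20% allowance would need 63 children, or 64 with equal arms, which is 3 or 4 more than stated.

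The consequence is small: by t-test, power at 24 per arm is 79.5% to 79.8%, against 81.2% to 81.4% at the stated minimum. These figures assume a two-sided test, the plan's own standard deviations and difference, losses shared equally between arms, and independent children, as in the article's calculation. Whole groups are randomised, and any effect of that on power would be additional; it is a separate question and this point does not rest on it. The sentence is wrong as written and should be corrected, but the error does not threaten the design.

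**What to change.** Correct the sentence in the Sample size section in one of these ways.

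1. Keep 60 and restate the allowance, for example: *60 children (30 per arm) will be recruited, which allows for the loss of up to 10 (16.7%), five per arm, while retaining 25 per arm.*
2. Keep 60 and the 20% figure, but state the result: *at 20% attrition 48 children (24 per arm) would remain, giving power of about 79.5% to 79.8%.*
3. If a full 20% allowance is wanted, change the target to 64 (32 per arm), and change the 60 in the Abstract and the Randomisation section to match.

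The first two options reword one sentence and leave recruitment and analysis as they are. The third costs four more children. The first is enough.
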